##### Statistical analyses for secondary and other endpoints

Repeatedly measured continuous secondary endpoints will be analysed using the same model as the safety co-primary endpoint. Count endpoints will be analysed with a generalised linear mixed model and a negative binomial distribution, accounting for the cluster’s random effect and observation time as an offset. Binary endpoints assessed at the end of the follow-up period will be analysed using mixed-effects logistic regression, adjusted for observation time, and including the cluster’s random effect. Cost-effectiveness analysis will employ generalised structural equation models. Finally, a descriptive summary of all pre-specified SAEs and deaths will be provided.

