### Follow-up

Follow-up will start the day of the delivery of the intervention (ie, delivery of the intervention materials to GPs), which should be within 30 days after cluster randomisation. In the control group, follow-up will start 15 days after cluster randomisation. Participants in both groups will be followed for 1 year, with data collection occurring at baseline and at 3, 6, 9 and 12 months after the start of follow-up. A detailed timeline for both trial arms is shown in online supplemental A figure S1.

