#### Secondary endpoints

The secondary endpoints are multifaceted: total number of medications prescribed during the trial measured using unique Anatomical Therapeutic Chemical codes, reduction of at least 50% of the prescribed PPI dose, PPI discontinuation (defined as a stop in PPI prescription as indicated by the GP), PPI sustained discontinuation (defined as 3 months without prescribed PPI), a switch to on-demand use, or use of alternative anti-reflux treatments, individual components of the RDQ (regurgitation, heartburn, dyspepsia) and atypical gastrointestinal symptoms measured by the Reflux Symptom Index (RSI).^31^ The RSI scales for each individual item ranges from 0 (no problem) to 5 (severe problem) points, with a maximum of 45 points. Further, we are interested in the occurrences of additional safety outcomes such as ulcers and/or gastrointestinal bleedings, nutritional deficiencies due to PPI overuse, such as vitamin B12, iron, magnesium or sodium, as well as other comorbidities, such as osteoporosis, small intestinal bacterial overgrowth, anaemia, fractures, nephritis and intestinal infections as reported by the GP. Furthermore, we will measure the QoL using the European Quality of Life-5-Dimensions 5-Levels (EQ-5D-5L) questionnaire.^32^ Each of the five dimensions (mobility, self-care, usual activities, pain/discomfort and anxiety/depression) has five levels (no, slight, moderate, severe and extreme problems) out of which one overall utility measure on a scale of 0 (worst health/death) to 1 (perfect health) will be derived using published algorithms.

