#### Statistical analysis

##### Statistical analyses for co-primary endpoints

To address the effectiveness, we will first quantify the change in prescribed PPI dose over the 12-month follow-up period. This will be done in two steps: (1) estimating the average PPI dose over the 12 months of follow-up, by dividing the area under the curve by the observation time and (2) calculating the relative change from baseline as one minus the ratio between the average prescription and the baseline prescription. Subsequently, the difference in the change in prescribed PPI dose between the control and intervention group will be calculated using a linear model, adjusted for the baseline dose and including a random effect for the cluster. We will use an intention-to-treat (ITT) analysis as primary analysis, and a per-protocol analysis as a secondary approach.

To address safety, the difference in the change in upper gastrointestinal symptoms between the two groups will be calculated with a repeated-measures linear mixed-effects model, adjusted for baseline values, and including the intervention group, the timepoint, and the interaction between group and timepoint as fixed effects. Effects of the cluster and participant will be added as random effects. We will conduct both ITT and per-protocol analyses. To claim success for the safety co-primary endpoint, both ITT and per-protocol analyses need to meet non-inferiority.

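### Binary secondary endpoints are adjusted for observation time, a post-randomisation variable, and not for baseline PPI dose: usually a small effect, and nearly free to put right

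*Protocol article*

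**What the plan says.** Under *Statistical analyses for secondary and other endpoints*, the protocol article fixes the binary model: "Binary endpoints assessed at the end of the follow-up period will be analysed using mixed-effects logistic regression, adjusted for observation time". Cluster enters as a random effect. No baseline covariate is named. In the same paragraph, count endpoints are modelled "accounting for the cluster’s random effect and observation time as an offset".

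Both co-primary models use baseline information. The effectiveness model is "adjusted for the baseline dose and including a random effect for the cluster". The safety model is a "repeated-measures linear mixed-effects model, adjusted for baseline values", and repeated continuous secondary endpoints inherit it.

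The binary endpoints tied to PPI dose are listed under *Secondary endpoints*: "reduction of at least 50% of the prescribed PPI dose, PPI discontinuation" and sustained discontinuation, which needs three PPI-free months by prescription.

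On follow-up, "Participants in both groups will be followed for 1 year". The section on missing data expects little of it. No dropout rate is given, nor any figure for how strongly baseline dose predicts stopping.

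**The concern.** Realised observation time is not a baseline characteristic. Withdrawal or death sets it, and both can depend on the arm and on what happened to the prescription. Conditioning on such a variable can move the odds ratio away from the randomised comparison.

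Arm-related exit is conceivable here. The trial is open-label, the intervention encourages stopping and anticipates rebound symptoms, and participants may withdraw at any time.

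A linear term in time on the logit scale is also not an exposure correction. Someone observed for less than three months cannot meet the definition of sustained discontinuation, whatever the coefficient. The count model treats the same variable as exposure, so the two neighbouring models are not aligned.

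Separately, baseline dose is collected, is used in the effectiveness model, and is a natural predictor of a halved or stopped prescription, yet it is absent here.

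Discontinuation matters more than most secondary endpoints, because the effectiveness sample size was calculated on it (10% v 25%).

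**Working it through.** **1. The plan's own figure.** Inputs from *Sample size*: 10% v 25%, two-sided alpha 0.05, power 90%, ICC 0.05, 80 clusters, mean cluster size 4.0, CV of cluster size 0.5.

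- Per arm without clustering: [1.96·√(2·0.175·0.825) + 1.2816·√(0.10·0.90 + 0.25·0.75)]² / 0.15² = (1.053 + 0.675)² / 0.0225 ≈ 133.
- Design effect: 1 + [(1 + 0.5²)·4.0 − 1]·0.05 = 1.20.
- Total: 2 × 133 × 1.20 = 319, against 316 stated. The figure reproduces.

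Nothing below changes it.

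**2. When does observation time vary?** The planned length is 12 months in both arms. The different start rules (delivery of materials, which should be within 30 days of randomisation, v day 15) move the origin, not the length. Variation therefore comes only from early exit.

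**3. Exit that follows the outcome.** All exit rates are assumptions. Simulation with no true effect: equal discontinuation hazard in both arms, a share of intervention-arm stoppers leaving within 2 months of stopping, 5% background dropout, clustering ignored.

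| Intervention stoppers who leave | Total early exit | OR unadjusted | OR adjusted for time, at event rates 10% / 17.5% / 25% |
|---|---|---|---|
| 10% | – | about 1.00 | about 1.00 |
| 30% | 6–8% | about 1.00 | 0.97 / 0.96 / 0.94 |
| 50% | 7–11% | about 1.00 | 0.91 / 0.87 / 0.85 |

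- If 30% of stoppers leave in *both* arms: 0.993 unadjusted, 0.994 adjusted (17.5% stoppers).
- If background dropout is 10% rather than 5%, the 30% case weakens: 1.018 unadjusted, 0.996 adjusted (17.5% stoppers). Across event rates and both dropout levels, the 30% case spans about 0.94 to 0.99.

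**4. Size against sampling error.** With 180 per arm at 10% v 25%, SE of the log-OR = √(1/18 + 1/162 + 1/45 + 1/135) = 0.30 before clustering. An OR of 0.95 is a shift of 0.051, about one sixth of an SE. In the worst cell (50% leave, 25% events in both arms), SE = √[2·(1/45 + 1/135)] = 0.243 and the shift is ln 0.85 = −0.163, or 0.67 SE. The simulated null rejection rate there rises from 4.8% to 10.9% at n = 360.

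**5. Exit that follows arm and prognosis.** Assumed: 80 clusters, about 400 patients, latent-scale ICC 0.05, outcome known for everyone, cluster-robust logistic regression in place of the mixed model, no true effect.

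- 5% exit unrelated to arm or prognosis: shift about 0.
- 5–10% exit related to arm (log-OR 0.7) and prognosis (log-OR 1.0 per SD): +0.02 to +0.03 on the log-OR scale.
- 20% exit strongly related to arm (log-OR 1.4): +0.08 to +0.09. Null rejection goes from 5.3% to 6.6%, or from 4.2% to 5.3% with prognosis log-OR 2.0.

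The sign is opposite to step 3, so the direction depends on the exit mechanism.

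**6. Adding baseline dose.** Same cluster set-up, 10% v 25%, prognostic strength assumed:

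| Log-OR per SD of baseline dose | Power at N ≈ 317, without → with | Power at N ≈ 397, without → with |
|---|---|---|
| 0 | 92.1 → 91.9% | 96.3 → 96.4% |
| 0.3 | 90.9 → 91.4% | 96.9 → 97.0% |
| 0.5 | 92.3 → 92.5% | 96.9 → 97.3% |
| 0.8 | 92.5 → 93.8% | 97.0 → 98.3% |
| 1.2 | 91.6 → 95.3% | 96.6 → 98.3% |

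A simpler scenario ignoring clustering (n = 360, OR 2.2, control rates 30% at high and 8% at low baseline dose) gives 82% → 86%. Larger gains would need a very strongly prognostic baseline dose.

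**The case against.** The strongest reply is that the covariate is nearly constant by design. Follow-up is 12 months in both arms and little missing data is expected. The ethics section says medication can be resumed at any time during the study, so returning symptoms do not force a withdrawal. The visible biases need large, one-sided, outcome-driven exit for which the document gives no rate. They shrink with ordinary dropout and change sign with the mechanism. This stands: a reader might infer that the covariate breaks the randomised comparison, and the document does not support that.

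A reader might also infer that leaving out baseline dose biases the result or has been shown to cost power. Neither follows. Omitting a prognostic covariate leaves a randomised comparison unbiased and only changes whether the odds ratio is marginal or conditional. The power loss depends on a prognostic strength that the document does not give, and no power is claimed for the secondary analyses. Baseline dose also has no obvious role for ulcers or bleeding.

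Replacing the covariate by a log-time offset or a time-to-event model is no clean cure. Both still use post-randomisation time. Time to first stop is not status at the end of follow-up, and non-informative censoring would be assumed. This stands too, and limits such models to a supportive role.

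What does not stand is that the article merely leaves detail to the analysis plan. It names the adjustment variable for the binary endpoints, and the one it names is post-randomisation.

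**Conclusion.** The point holds as a minor one. Adjusting for observation time has little to offer: it is close to inert when few leave early, and can mislead in an unpredictable direction when exit depends on arm and outcome. The bias is negligible under the article's expectation of few missing data. It is about 1% to 6% on the odds ratio if 30% of intervention stoppers leave, and 9% to 15% if 50% do with 5% background dropout. These rates are assumptions, and the simulations behind them ignore clustering. Omitting baseline dose is a modest efficiency matter for the dose-related binaries only, roughly 0 to 4 power points over most of the assumed range. The sample size and both co-primary analyses are untouched.

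**What to change.** For at least 50% dose reduction, discontinuation and sustained discontinuation, specify the main analysis as a mixed-effects logistic model with group and baseline PPI dose as fixed effects and cluster as a random effect, without observation time. Then:

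- keep the observation-time-adjusted model as a sensitivity analysis;
- deal with early exit through the approach already set out under *Handling of missing data*;
- if wanted, add a time-to-event analysis, or a complementary log-log model with log observation time as offset, as supportive only, stating that it targets a different estimand and assumes non-informative censoring.

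Cost: a change of wording and slightly more analysis work, with no new data. The odds ratio becomes conditional on baseline dose, which should be stated when it is reported.

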##### Handling of missing data

Even though we assume very few missing data, if there is a substantial amount of missing data, we will consider multiple imputation by chained equation and analysing the available cases as a sensitivity analysis. If the missingness is limited and expected to not confound the interpretation of results, we will disregard the missing data and perform an analysis of the available cases.

### Methods: safety monitoring and public and patient involvement

#### Safety monitoring

Collection, reporting and investigation of SAEs, as well as notification to the ethical committee will be conducted following the applicable regulation and approved process. Conversely to SAEs, reporting of non-SAEs is not mandatory and will be done at the discretion of the treating physician.

To ensure the safety of our participants, we plan to conduct one interim analysis after the first 200 participants are followed for at least 6 months after inclusion. The safety parameters that will be considered in this interim analysis include the RDQ, gastrointestinal ulcers, gastrointestinal bleeding and all SAEs in each group. The advisory board will evaluate unblinded data and provide recommendations.

In addition to the trial’s safety monitoring, we have included relevant adverse events within the primary and secondary safety endpoints.

#### Patient and public involvement

The study is supported by both an advisory board and a stakeholder group. The advisory board is composed of experts in PPI (de)prescribing. They offer guidance on study design, provide perspectives on specific elements, and serve as an independent data safety committee, evaluating participant safety and advising on trial modifications or termination if safety concerns arise. The stakeholder group, made up of clinical professionals and patient representatives, provides input on the trial design and intervention materials aimed at GPs and participants. Additionally, the DROPIT intervention has been developed with repeated input from patients/citizens and GPs.

## Discussion

The findings from this study will provide evidence on the effectiveness and safety of the DROPIT PPI deprescribing intervention. Successful implementation of our PPI deprescribing strategy could improve patient outcomes by reducing unnecessary adverse effects, such as infections, fractures or nutrient deficiencies, while ensuring appropriate, evidence-based treatment. Additionally, it could promote rational medication use, reduce polypharmacy, and minimise healthcare costs and resource utilisation. To our knowledge, this is the first randomised controlled PPI deprescribing trial in the primary care setting of Switzerland.

We chose a cluster-study design to prevent contamination that could arise if GPs were to treat participants in both the intervention and control groups.^42^ However, we recognise that cluster trials can introduce selection bias, as participant recruitment typically occurs after randomisation.^43 44^ To mitigate this, recruitment in our trial will cease once a cluster is closed, after which participants will be assigned to the intervention or control group based on their GP’s random assignment. It is unlikely that patients will avoid visiting their GP due to prior knowledge of the trial.

The 12-month follow-up period is consistent with similar studies and should be sufficient to capture potential rebound symptoms.^45^,^48^ Nevertheless, there is a small risk that we might miss the reoccurrence of GI bleeding or ulceration that might occur at a later time point, mainly because we are following the participants from the time we deliver the intervention to the GPs, which does not necessarily coincide with the timing of deprescribing. However, with a 12-month follow-up, and expecting that deprescribing will be done earlier rather than later during that time, we expect to observe the participant after the deprescribing.

Finally, we recognise that participants may receive new diagnoses during the follow-up period that justify PPI use, potentially no longer fulfilling the initial eligibility criteria. However, since this reflects typical clinical variations and occurs after randomisation, we will not exclude these participants. Instead, we may conduct a sensitivity analysis for the co-primary endpoints, where these participants will be censored.

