## Ethics

We greatly value and respect the contributions of those who share their clinical data and insights from practice with us. We are fully committed to upholding their rights, which include ensuring privacy, obtaining informed consent (online supplemental B), and respecting their right to withdraw from the study at any time. GPs who recruit patients are financially compensated for their time and expertise as healthcare professionals involved in the study. While many patients join the study out of a desire to contribute to research, we also expect that, as users of PPI medication, they may experience direct benefits from participating. The risks in this study are minimal, as deprescribing is part of routine clinical practice, and the study intervention does not require any measures beyond this. Resuming medication is possible at any time during the study, and participants can withdraw from the study at any time. Additionally, in our efforts to create social value, we actively involve a range of stakeholders in our decision-making processes to ensure that diverse perspectives are considered (see the Patient and public involvement section). The study will be conducted in accordance with principles in the current version of the Declaration of Helsinki,^50^ the relevant parts of the guidelines of Good Clinical Practice (GCP) from the International Council for Harmonisation (ICH), as well as local regulations. This study has been approved by the Ethics Committee of Bern, Switzerland (BASEC ID: 2024-00685).

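### The optional sensitivity analysis censors at any new PPI-justifying diagnosis, including those that stopping the PPI could cause, so it cannot show that the co-primary results are robust

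*Protocol article*

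**What the plan says.** The Discussion foresees that "participants may receive new diagnoses during the follow-up period that justify PPI use". For the main analysis these participants stay in: "since this reflects typical clinical variations and occurs after randomisation, we will not exclude these participants". The next sentence adds the optional analysis: "Instead, we may conduct a sensitivity analysis for the co-primary endpoints, where these participants will be censored". The trigger is any new PPI-justifying diagnosis, and no distinction is drawn by cause.

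Four other places bear on this:

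- Secondary endpoints lists "additional safety outcomes such as ulcers and/or gastrointestinal bleedings", and the Safety monitoring section makes ulcers and bleeding interim safety parameters.
- An earlier paragraph of the Discussion concedes that "there is a small risk that we might miss the reoccurrence of GI bleeding or ulceration that might occur at a later time point".
- The Ethics section states: "Resuming medication is possible at any time during the study".
- Under Statistical analyses for co-primary endpoints, the dose endpoint is built by "estimating the average PPI dose over the 12 months of follow-up, by dividing the area under the curve by the observation time", then taken relative to baseline. The RDQ is analysed with a repeated-measures mixed model.

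**The concern.** Some diagnoses that justify a PPI are also possible consequences of stopping one. The Introduction names reflux disease, reflux oesophagitis and NSAID-associated ulcers among the conditions PPIs treat, and the trial watches for ulcer and bleeding after deprescribing. The sample size section assumes 25% discontinuation with the intervention against 10% in control. A diagnosis caused by withdrawal would then be expected more often in the intervention arm. It would also be made by a GP who knows the allocation.

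Censoring at such an event conditions on something that treatment may have produced. On dose, it removes the period after the PPI is restarted and keeps the low-dose period before it. On the RDQ, a non-inferiority safety endpoint, it drops scores from the time of a possible harm. Agreement between this analysis and the main one could then be reported as robustness when it shows nothing of the kind.

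**Working it through.** The plan gives no figure for this point. Its sample sizes (316 and 360) do not depend on it. The check concerns direction and possible size.

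**Dose endpoint.** Score = 1 − (area under the dose curve ÷ observation time) ÷ baseline dose. Set the baseline dose to 1. Suppose the PPI is stopped at month s and restarted at full dose when a diagnosis is made at month r.

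- All data: 1 − (s + 12 − r)/12 = (r − s)/12
- Censored at r: 1 − s/r = (r − s)/r

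The censored score is 12/r times the uncensored one, so for this kind of patient it is always larger when r is below 12.

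| s | r | All data | Censored | Gain |
|---|---|---|---|---|
| 2 | 5 | 1 − 9/12 = 0.25 | 1 − 2/5 = 0.60 | 0.35 |
| 1 | 3 | 0.167 | 0.667 | 0.50 |
| 1 | 4 | 0.25 | 0.75 | 0.50 |
| 1 | 6 | 0.417 | 0.833 | 0.417 |
| 3 | 6 | 0.25 | 0.50 | 0.25 |
| 3 | 9 | 0.50 | 0.667 | 0.167 |

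The documents give no rate of such events. If 2% to 10% of the intervention arm were affected (an assumption), the arm mean would rise by between 0.02 × 0.167 = 0.003 and 0.10 × 0.50 = 0.05.

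Not every patient moves the contrast this way. A control patient whose dose doubles at month 6 scores 1 − (6 + 2 × 6)/12 = −0.50 with all data and 0 when censored, which shrinks the difference between arms. A patient whose dose never changes scores the same either way.

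**RDQ endpoint.** The direction was checked by simulation under assumed inputs: a 1.5-point worsening in affected patients, 10% affected with the intervention and 2% in control, and visits at 3, 6, 9 and 12 months. The mixed model had a participant random intercept and no cluster effect, with 3000 per arm and three replicates. The table shows the month-12 difference, intervention minus control, where higher is worse for the intervention.

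| Symptom pattern | All data | Censored | Shift |
|---|---|---|---|
| Worse only from diagnosis on | 0.098 | −0.033 | −0.13 |
| Worse before and after | 0.098 | 0.053 | −0.05 |
| Worse before, settles on restart | −0.030 | 0.053 | +0.08 |

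The levels carry simulation noise: in the last row the true all-data difference is 0 and −0.030 was obtained. The shifts come from the same simulated data and are the part to read. Two patterns favour the intervention. The third goes against it, because the model carries the high scores before the diagnosis forward. With 5% affected in both arms, the two patterns run (first and last rows) showed no material shift. If censoring meant removing the participant altogether, the shift at 10% against 2% was about −0.13 or nil. For scale, the non-inferiority margin is 0.5 points.

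**The case against.** The strongest reply is that this analysis decides nothing and may never be run. That stands. The wording is permissive, and the Discussion keeps these participants in. Effectiveness rests on ITT, safety success requires ITT and per-protocol, and the censored analysis is part of neither rule. It is also not the only robustness check, since Handling of missing data describes another.

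Three further points stand in part:

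- The remark about typical clinical variation is given as the reason for retaining participants. The text does not claim that every new diagnosis is unrelated to treatment. It simply draws no line.
- Which diagnoses count as justifying a PPI is set in supplementary tables that are not shown, and a separate analysis plan may define the censoring. The eligibility criteria also exclude certain combinations of bleeding-risk drugs and risk factors, so a high rate of ulcer or bleeding cannot be presumed.
- Harms are captured elsewhere, as secondary safety outcomes and at the interim review, so a harmed patient does not vanish from the safety evidence.

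A reader might infer that the censoring pushes both co-primary endpoints towards success. The documents do not support that. The RDQ shift takes either sign depending on when symptoms occur, dose increases in control patients work the other way, and any difference by arm rests on event rates that are not given.

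**Conclusion.** The concern holds in a limited form. The stated rule would censor at events that may follow from deprescribing, so the censoring is potentially informative and arm-dependent. For patients who stop and restart, it inflates the dose reduction (0.35 in the main example, 0.17 to 0.50 across the other timings tried). For the RDQ it discards data after a possible harm, with a bias of uncertain sign. An analysis with these properties cannot serve as evidence of robustness.

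The net effect on the trial is unknown. The illustrations, up to about 0.05 on the mean dose score and 0.13 RDQ points, rest entirely on assumed event rates and symptom patterns. The analyses that decide the endpoints are untouched. This is a cheap improvement of low to moderate importance.

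**What to change.** If the analysis is run:

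1. Keep all RDQ data after the new diagnosis.
2. In the dose analysis, censor only at a prespecified list of new indications that PPI withdrawal cannot plausibly cause, and do not censor at diagnoses that it could cause, such as ulcer, bleeding or reflux disease. Because GPs and analysts are not blinded, fix the list before any data by arm are seen, including at the interim analysis.
3. Label the analysis supportive only.
4. Whether or not it is run, report new PPI indications by arm and type.

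The cost is protocol or analysis-plan wording. Diagnoses and medications are already collected from GPs, and no change to design, sample size or data collection is needed. The small downside is that a few diagnoses have to be classified.
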